#### Radiation simulation and diagnostic mpMRI

A CT simulation will be performed with 3 mm slice thickness that will be used for planning. Simulation will occur with a custom MRI compatible immobilization mold (Fig. 3). The isocenter, along with 1.5 to 3 cm increments superior/inferior along the sagittal plane of the isocenter, will be marked over the extent of gross disease. An additional lateral mark will be placed to control for rotation. The markers utilize a radiopaque BB, which is imaged during the second CT scan, with intravenous (IV) contrast when possible. The BB locations are then tattooed to serve as localization markers during biopsy and scar removal at the time of surgery. Diagnostic mpMRI sequences will all be performed on a Siemens 3T Vida magnet (Siemens AG, Munich, Germany). The mpMRI sequences will be fused to the CT simulation scan and used to identify radiomic habitats for biopsy and direct treatment planning. Patients are treated on combination MRI linear accelerator (MRL) when possible. When treating on the MRL, a true fast imaging with steady-state free precession (TRUFI) [41] sequence will be obtained on the 0.35T MRIdian System (ViewRay Inc., Oakwood Village, OH, USA), that will be used for treatment planning, utilizing the CT from simulation for electron density.

**Fig. 3 Fig3:**
[figure not shown]
Example of the custom MRI compatible immobilization for a left thigh STS. BB marks on the left anterior thigh will then be tattooed to serve as a guide for setup (e.g., imaging, daily treatment) and habitat directed biopsy that will be used for exploratory genomic studies

#### MRI radiomic habitat determination, target definitions

A pretreatment diagnostic mpMRI will be performed to obtain T_2_ short tau inversion recovery (STIR), DWI, and DCE sequences. These sequences will be used to delineate three separate habitats. The gross tumor volume (GTV) will be delineated from the T_1_ post contrast scan, which is combined with STIR (e.g., peritumoral edema), determines the clinical target volume (CTV). This GTV will then be stratified on a per pixel basis to identify three habitats based on ADC intensity (as calculated from DWI) and the rate/magnitude of the DCE (K^trans^). The median value will be used as the dichotomization threshold to define the high (e.g., High ADC) and low (e.g., Low ADC) intensity regions (Fig. 4). The overlay of these sequences will result in three separate and non-overlapping habitats:

**Fig. 4 Fig4:**
[figure not shown]
MRL planning shows the GTV on a TRUFI image (**A** and **C**), is rigidly mapped onto an ADC (**B**) and DCE (**D**) sequence to determine the low and high ADC/DCE regions. The regions of high and low overlaps based on median value (**E**: axial view; **F**: sagittal view; **G**: coronal view) are then used to determine habitats 1, 2, and 3

Habitat 1: Low ADC/Low DCE: high cell density with hypoxia (i.e., the most radioresistant habitat).Habitat 2: Low ADC/High DCE: high cell density that are well oxygenated.Habitat 3:
High ADC/Low DCE: necrosis and fluid, low tumor cellularity.High ADC/High DCE: necrosis and fluid, low tumor cellularity.

The three habitats will receive 50 Gy (GTV50), 60 Gy (GTV60), or 70 Gy (GTV70). GTV50 will consist of gross tumor defined by MRI T_1_ post contrast images and the areas of the gross tumor defined above in habitat 3 will receive 50 Gy in 25 fractions. GTV60 will receive the intermediate dose escalation portion of the gross tumor defined by Habitat 2 and GTV70 will receive the high dose escalation portion of the gross tumor defined by habitat 1, with 60 and 70 Gy in 25 fractions, respectively.

The clinical target volumes (CTVs) take neighboring organs at risk (OARs) into account. For habitat 3, the standard radiation dose and fractionation to 50 Gy will encompass the volume of gross and microscopic disease. Typically, the CTV50 will equal the GTV plus a 3 cm margin along the length of the muscle, commonly longitudinal (proximal and distal directions), with a 1.5 cm radial margin expansion, including suspicious edema (as defined on the T_2_ STIR images) up to 4 cm beyond GTV. The CTV margin will respect anatomic barriers (e.g., compartment, bone, skin). CTV60 and CTV70 correlate with habitat 2 GTV60 (i.e., Low ADC/High DCE) and Habitat 1 GTV70 (i.e., Low ADC/Low DCE) volumes, after removing small volumes < 5 cc (or < 0.1 to 1 cm [2]) and subtracting from planning organs at-risk volume (PRV). To minimize toxicity risk, a PRV of normal structures will be created (e.g., bone, joints, organs, major neurovascular structure, and skin surface), expanded either 10 to 15 mm or 5 to 10 mm and contoured out of CTV70 and CTV60, respectively.

An alternative approach can be employed at the discretion of the treating physician, where a single Low ADC volume would be created, combining habitats 1 and 2 for dose escalation. Then small volumes that are < 5 cc (or < 0.1 to 1 cm [2]) would be removed and dosing is based on proximity to OARs. Dosing for the CTV70 would be created from this low ADC volume after excluding the PRV (with a margin of 10 to 15 mm) of normal structures (e.g., bone, joints, organs, major neurovascular structures, and skin surface). CTV60 would then be the remaining volume after removing PRV of normal structures plus 5 to 10 mm.

The PTVs includes the CTV plus error of setup and organ motion. Typically, the PTV will equal the CTV plus 3 to 5 mm depending on setup, but PTV as low as 1 mm can be used if real-time tracking is employed. Daily image-guided radiation therapy (IGRT) is encouraged to minimize daily setup errors, preferably a cone beam CT or MRI. The biopsy clips assist in image-guided localization to ensure accurate daily setup for radiation treatment delivery.

Skin surfaces are not to be contoured in CTVs or PTVs unless grossly involved with tumor, and the use of bolus on the skin is discouraged.

#### Normal tissue constraints

Radiation to normal tissue will be administered under accepted normal tissue tolerances, with efforts made to avoid treating the full circumference of an extremity, anogenitalia (e.g., scrotum, testis, vulva, and anus), skin over commonly traumatized areas (e.g., elbow and knee), and weight-bearing bones (e.g., femoral head and neck) (Table 2).

**Table 2 Tab2:** Normal structure dose constraints

Structure	Constraint
Anus	V30 Gy < 50%
Genitalia	V30 Gy < 50%
Joint	V50 Gy < 50%
Femur	V50 Gy < 50%
Testes	V3 Gy < 50%
Skin Strip	V20 Gy < 50%
Kidney	V14 Gy < 50%
Femoral head/neck	V60 Gy < 5%
Lung	V20 Gy < 20%
Spinal Cord	D0.03 cc < 45 Gy
Skin minus 5 mm	53.5 Gy (5 cc < 55 Gy)
Other normal structure	Tolerated dose 5/5

Efforts to limit dose near neighboring structures will be made, limiting with no more than 50% of the anogenital structures (e.g., anus and genitalia) receiving 30 Gy; 50% of joints or weight-bearing bones (e.g., shoulder, hip, elbow, femur, and knee) receiving 50 Gy; 50% of a skin strip (longitudinal strip of skin and subcutaneous tissue with a minimum of 2 cm in length) receiving 20 Gy; 50% of the kidney receiving 14 Gy; and 50% of the testes receiving 3 Gy (in patients preserving fertility). No more than 5% of the femoral head/neck should receive 60 Gy. No more than 20% of the lung should receive 20 Gy. For any other normal tissue structures, radiation doses should be limited to the established tolerated dose 5/5 for these structures. In addition to standard structures, additional structures that were monitored included neurovascular structures (e.g., femoral neurovascular bundle, sciatic nerve, lumbosacral plexus), with a maximum point dose (0.03 cc) of 67 Gy. A wound flap, defined as the 3 cm of subcutaneous tissue flanking 3 cm beyond the wire/scar, was limited to a point max of 53.5 Gy and V30 < 50%, when possible. If these constraints cannot be met, then techniques to improve dosimetry will be considered. Variations of these constraints will be acceptable if approved by the treating physician.

#### Treatment planning and plan adaptation

The patients will be planned to undergo neoadjuvant external beam radiation by using the intensity-modulated radiation (IMRT) technique, with a SIB to 70 Gy, 60 Gy, and 50 Gy in 25 fractions for habitats 1, 2, and 3, respectively. Each PTV will be prescribed to cover 95% of the respective volume receiving 100% of the respective prescription dose.

There is 1 planned adaptations using mpMRI sequences (via Siemens 3T Vida magnet) that occur during treatment, and additional adaptations can be considered for unexpected tumor volume changes, especially day 1 of treatment to account for volumetric changes that occurred from the time of simulation (Fig. 5). The planned adaptation uses a diagnostic mpMRI taken two to three weeks into treatment, where new habitats will be created and dose-adapted based on the tumor’s early response to treatment. To properly account for alterations within the habitats, the initial ADC and K^trans^ median values are then normalized to account for differences between the two scans. The normalization factor for K^trans^ is the average signal for the same adjacent uninvolved vessel (1 cm in length) between the initial and second mpMRI. For ADC, a vial with a known ADC value is placed for each mpMRI, and the average signal for a 1 cm radius sphere is used to normalize between the initial and second mpMRI. The vial contains a 50% concentration of polyvinylpyrrolidone, and the ADC value is calculated to be 278 × 10^− 6^ mm^2^/s assuming an ambient operating temperature of 22 °C (the typical temperature within the vault).

**Fig. 5 Fig5:**
[figure not shown]
Adaptation at fraction 1 (**B**) to account for tumor growth from the time of simulation (**A**). Solid green line represents GTV at time of simulation and dotted green line represents GTV at time of fraction 1

#### MRI habitat-directed biopsy and clip placement

Once the habitats are identified from pretreatment imaging, patients are then referred to interventional radiology for an image-guided biopsy and fiducial placement in the three habitats. This will validate the biopsy locations, aid in daily image guidance during treatment delivery, and assist in pathologic identification of each habitat after surgical resection.

Prior to the day of biopsy, the patient images will be reviewed in tandem by the radiation oncologist and interventional radiologist. On the day of the biopsy, active coordination between the interventional radiology team and the radiation oncology team, including nursing, radiation therapy, and physicians, will ensure real-time targeting of the three habitats from the planned entry sites. The patient’s mold used for CT simulation will be placed on the CT biopsy machine, ensuring the patient is in the exact position as during simulation. The RT planning tattoos, serving as entry sites for the biopsy, will be strategically chosen for each habitat to ensure precise needle insertion and to reduce the risk of seeding. Biopsy will be performed under moderate sedation using intravenous midazolam and fentanyl, as per institutional policy. Scout images will be obtained with radiopaque BBs placed at the same levels as the RT planning tattoos. The biopsy sites are planned to be included within the surgical resection bed to mitigate the risk of seeding, as STS are known to possibly seed biopsy tracts. During the biopsy, each habitat biopsy’s details, including size of needle, number of passes, and type/number of clips, will be meticulously recorded by the radiation oncologist while the interventional radiologist performs the procedure. Each set of clips will represent an intra-tumoral habitat and will be used during daily RT setup to ensure proper target coverage. The biopsy tract images will be used by the surgeon to ensure all needle tracts are resected at the time of surgery. Habitat tissue will be preserved as fresh frozen samples for future studies.

### Radiological and pathological treatment evaluation

Post-RT diagnostic mpMRI will be performed within three to eight weeks after the completion of radiation, with the same immobilization and sequences as the pre-treatment mpMRI. This will be used to assess radiographical treatment response, surgical planning, and for future delta radiomics.

After post-treatment mpMRI, resection of the tumor will occur between three to twelve weeks after the completion of radiation therapy. The findings will be correlated to final surgical pathology reports after resection of the tumor and response of each habitat (Fig. 6). The remaining viable cells and margin status will be evaluated by a designated sarcoma pathologist. This evaluation will be used to estimate the pathologic response overall, in addition to the level of response within each habitat. A FPR is 1-% viable malignant cells, with “response” including necrosis, treatment response, and fibrosis.

**Fig. 6 Fig6:**
[figure not shown]
Specimen radiograph displaying markers for each habitat and to help orient with preoperative imaging (**A**). At time of pathological evaluation, the specimen is mapped to a grid to determine percentage of pathological response throughout the specimen (**B**)

The pathologists on this study are sarcoma specialized, and cross-review is performed on all cases by a fellow sarcoma specialized pathologist. No molecular markers or assays are required to assess pathologic response, as it is a microscope-based assessment. To help the pathologist ascertain which part of the tumor they are analyzing, the 3 habitats biopsied before the start of RT will be designated with specialized clips in each location (minimum of 1.5-3 cm apart) (Fig. 7). A radiograph is completed on the resected pathologic specimen, to orient the pathologist and determine the habitat locations for intratumoral response analysis. The entire tumor is analyzed for pathologic response along with each habitat marked with clips. The pathologists also mark off the sections that had viable cells remaining (Fig. 6), so future radiomic-dose correlations can be determined, which will account for cumulative dose and spillover.

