#### Primary endpoint

The rate of FPR (tumor response ≥ 95%) at the time of surgery.

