#### Secondary endpoints

Margin status estimate as defined as the final tumor margin of the surgical specimen will be conducted by pathologist. A clear margin (R0) or a positive margin (R1/R2) will be designated, along with the location of the margin, which will be radiographically correlated to the habitat.Pathologic response of each habitat delineated on pathology specimen as determined by the difference in tumor response by various heterogenous portions of the tumor, as delineated by MRI-directed pre-RT clip placement.Rate and types of adverse events evaluated during weekly on-treatment visits (OTVs) up to 4 months (< 120 days) post-surgery.Disease control, determined as the absence of local tumor progression, to be per assessment of the treating radiation oncologist (i.e., clinical assessment) and radiologist (i.e., radiological assessment) for up to 4 months after surgery.Survival, as assessed by clinical visit, virtual visit, or telephone visit for up to 4 months after surgery.

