**Fig. 7 Fig7:**
[figure not shown]
Example of stereotactic biopsy within a habitat of the posterior thigh. (**A**) MRI identification of Habitat 1 (blue) target. To account for sofit tissue rotation, needle insertion is designated at the proximal tattoo (BB#1) and a depth of 7 cm towards the center of the femur is measured, with a medial tangential 5.5 cm line (90 degrees), creating the final biopsy track 9 cm from the surface. (**B**) CT measurements, biopsy, and clip placement are illustrated. Each site is defined by a different marker (e.g., one visicoil proximal biopsy, two visicoils at midpoint habitat, and one visicoil plus one helical mammotome for the distal habitat sampled). In addition to helping with daily set up, these markers will also be used at the time of pathological evaluation to orient the specimen and determine treatment response within each habitat

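### The per-habitat response score is open to reader expectation, because the pathologist is oriented to each habitat before a subjective reading and no masking is stated

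*Protocol article*

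**What the plan says.** Under *Secondary endpoints* the protocol article lists "Pathologic response of each habitat delineated on pathology specimen as determined by the difference in tumor response by various heterogenous portions of the tumor", with the portions identified by clips placed before radiotherapy. The *Primary endpoint* is a whole-tumour measure: "The rate of FPR (tumor response ≥ 95%) at the time of surgery".

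Several statements describe what the pathologist works from:

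- *MRI habitat-directed biopsy and clip placement*: one purpose of the clips is to "assist in pathologic identification of each habitat after surgical resection". The radiation oncologist records the type and number of clips at each site.
- *Radiological and pathological treatment evaluation*: the clips are there "To help the pathologist ascertain which part of the tumor they are analyzing". The section then adds: "A radiograph is completed on the resected pathologic specimen, to orient the pathologist and determine the habitat locations for intratumoral response analysis".
- Fig. 7 legend: "Each site is defined by a different marker". The example labels the sites by position (proximal, midpoint, distal). The legend says the markers also serve to determine response within each habitat.

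The same evaluation section says that response is read by microscope without any assay, and that "cross-review is performed on all cases by a fellow sarcoma specialized pathologist". It does not say whether either reader is masked, or whether the second reader sees the first score.

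**The concern.** A percentage of response judged by eye can drift towards what the reader expects. Habitat labels carry expectations. Habitat 1 is described as the most radioresistant, and by default habitats 1, 2 and 3 are planned to 70, 60 and 50 Gy. If the reader knows which habitat a site represents, the between-site difference may partly reflect that knowledge.

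At stake is a pre-specified secondary endpoint and the later work built on it. The *Discussion* plans to relate each habitat's response to the dose delivered there. The trial has a single arm, so no control specimens are read alongside that would show or offset a reading effect.

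**Working it through.** The article gives no figure for the habitat comparison, so the check is mainly a reading of its sections against one another.

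**1. Is the score subjective?** Yes. It is a microscope reading with no assay.

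**2. Does the workflow lead the reader to the habitat?** Three places point the same way: the biopsy section ("assist in pathologic identification of each habitat after surgical resection"), the evaluation section ("A radiograph is completed on the resected pathologic specimen, to orient the pathologist and determine the habitat locations for intratumoral response analysis") and the Fig. 7 legend. The natural reading is that habitat is known at scoring. That is an inference, since no sentence says the pathologist is told a habitat number or a dose.

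**3. Is there a stated guard?** No. Cross-review brings a second specialist, but the article does not call that read masked or independent.

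**4. Does habitat reveal dose?** Only under the default plan in *Treatment planning and plan adaptation* (70/60/50 Gy for habitats 1/2/3). Two provisions break the link:
- *MRI radiomic habitat determination, target definitions* allows habitats 1 and 2 to be merged, with 70 or 60 Gy then depending on distance from normal structures.
- The mid-treatment scan redraws the habitats and adapts the dose.

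**5. In which direction would expectation push?** The article does not settle it:
- Habitat 1 is the most resistant but is planned to the highest dose.
- Habitat 3 is planned to the lowest dose but is defined as necrosis and fluid, and necrosis counts as response.
- The Fig. 2 legend assumes an equal probability of response in every habitat.

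**6. Does it reach the primary endpoint?** No. That endpoint is one whole-tumour reading per patient, all patients receive the same strategy, and hiding the clip key leaves that reading unchanged. The only powered figure belongs to it. Exact binomial enumeration used these inputs:
- stages of 13, 10 and 13 (*Study design*; 13 + 10 + 13 = 36);
- success at ≥ 5 of 13, ≥ 5 of 23 or ≥ 7 of 36, and futility at ≤ 2 of 23 (*Sample size and interim analyses*).

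At a true rate of 24% the chances of success at the three stages are 0.1816, 0.4967 and 0.1404. Their sum is 81.9% after rounding, against the stated 81.8%. At 7.9% the type I error is 3.9%, within the 5% limit. Enrolment is 36 / (1 − 0.15) = 42.4, so 43, as stated. Masking the clips changes none of these.

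**7. Is masking feasible?** It appears so. Sites carry distinct markers, the example names them by position, and the clip record is made by the radiation oncologist rather than the pathologist.

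**The case against.** The strongest reply is that the article never says the pathologist knows the habitat. The markers could show only position, the radiation oncologist could hold the key, and the full protocol (version 1.4, not shown) may already mask the reading. A condensed article need not print a pathology worksheet. This stands as a limit on the claim. It does not dispose of it, because the point rests on a workflow the article does describe, whose stated purpose is to bring the pathologist to the habitats, and not on silence alone.

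A second reply is that masking cannot rescue the comparison. Baseline tissue differs between habitats, and necrosis may reveal habitat 3 under the microscope. That is true and limits what the fix can achieve. It is not a reason to leave reader expectation uncontrolled.

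A third is practical. The Fig. 6 legend says the markers help orient the specimen with preoperative imaging, so masking takes some care over what imaging is shown. This also stands, as a modest cost.

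**Conclusion.** The concern holds in a limited form. The described workflow orients the pathologist to habitat locations before a subjective score and states no masking, so the secondary per-habitat comparison can be biased by expectation. Size and direction are unknown. The conclusion assumes that the full protocol does not already mask the reading; if it does, one sentence in the article settles the matter.

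A reader might infer more than the documents support:

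- *That the reader knows the dose at each site.* Habitat fixes dose only under the default plan, and merging or adaptation can break the link.
- *That bias has been shown, in a known direction.* No order of response is predicted, and no reading data are given.
- *That the primary decision is exposed*, since 4 versus 5 of 23 or 6 versus 7 of 36 turns on one call. Those thresholds apply to the whole-tumour rate, which clip identity does not affect.
- *That this is the trial's only internal contrast.* *Data analysis* also relates margin status to habitat.

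**What to change.** State in the protocol that:

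1. The pathologist receives the specimen radiograph with marker codes or positions only. Any preoperative image used for orientation carries no habitat or dose contours.
2. Each clip site is scored by code.
3. Radiation oncology, which already records the clip details, keeps the code-to-habitat and dose key and releases it only after the site-level scores are locked.

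As an option, the existing cross-reviewer records a score before seeing the first one.

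The habitat results should also be reported with the caveat that habitat 3 starts as necrosis and fluid while necrosis counts as response, so some difference may precede treatment and the reader may be partly unmasked by the tissue.

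The cost is a revised worksheet, a change in the order of steps and some coordination at sign-out. No new staff or procedures are needed. A separately recorded second score adds a little work beyond the present cross-review. Sample size, power and the primary analysis are unchanged.
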